## Abstract

**Background:**

Autism spectrum disorder (ASD) is a neurodevelopmental disorder characterized by impairments of social interaction and communication as well as repetitive, stereotyped behaviour. Previous research indicates that ASD without intellectual impairment is associated with underactivity and reduced functional connectivity of the brain’s mentalizing pathway, to which the right temporo-parietal junction (rTPJ) serves as an important entry point and hub. In this study, we aim to utilize functional magnetic resonance imaging (fMRI) to localize activation maxima in the rTPJ and other regions involved in social cognition to generate individualized targets for neuro-navigated, intermittent theta burst stimulation (iTBS) in order to modulate brain activity in a region centrally engaged in social information processing.

**Methods:**

In this single-blind, randomized, between-subject neuroimaging-guided brain stimulation study we plan to recruit 52 participants with prediagnosed ASD and 52 controls without ASD aged between 18 and 65 years. Participants will be classified into two groups and will randomly receive one session of either verum- or sham-iTBS. Effects will be assessed by using well-established experimental tasks that interrogate social behaviour, but also use computational modelling to investigate brain stimulation effects at this level.

**Discussion:**

This study aims to use personalized, non-invasive brain stimulation to alter social information processing in adults with and without high-functioning ASD, which has not been studied before with a similar protocol or a sample size of this magnitude. By doing so in combination with behavioural and computational tasks, this study has the potential to provide new mechanistic insights into the workings of the social brain.

**Trial registration:**

German Clinical Trial Register, DRKS-ID: DRKS00028819. Registered 14 June 2022.

## Introduction

### Background and rationale

Autism spectrum disorder (ASD) is a neurodevelopmental disorder with an estimated lifetime prevalence of at least 1% and an onset in early childhood [1, 2]. ASD is characterized by qualitative impairments of social interaction and communication as well as stereotyped, repetitive behaviours and sensory abnormalities [1, 2]. A cardinal feature of ASD are deficits in social cognition, including impaired mentalizing [3]. Mentalizing or Theory of Mind (ToM) is the ability to interpret and predict behaviour by ascribing mental states to oneself and others [4]. Mentalizing deficits make it difficult for ASD individuals to quickly grasp others’ beliefs, intentions and emotional states and to adapt their behaviour accordingly during social interaction [4].

Experimental evidence from genetic linkage studies, animal models, functional neuroimaging and non-invasive brain stimulation (NIBS) has shown that ASD individuals show an aberrant cortical plasticity and activity profiles [5–9]. Here, dysfunction of the ‘neurocognitive pathway of mentalizing’ has been demonstrated [10–13]. Based on the insight from previous studies that brain activations differences in the mentalizing pathway might be more closely related to behavioural difficulties and social impairments in autism, we decided to use functional neuroimaging to generate personalized stimulation targets for TMS and to focus on rTPJ as it represents a key node of the mentalizing pathway [14, 15]. It has been proposed that a core feature of ASD without intellectual impairment are individual alterations in functional connectivity patterns. A correlation between the extent of the aberrant connectivity and behavioural symptoms in ASD has also been found [16]. Functional magnetic resonance imaging (fMRI) studies have shown abnormalities in activation and connectivity profiles of the right temporo-parietal junction in autism, supporting its role in situation-awareness and social perception [13, 17]. Moreover, impaired social cognitive abilities and alexithymia have been shown to correspond to reduced connectivity between the dorsomedial prefrontal cortex (dmPFC) and the TPJ [18]. In addition, hypoactivation of the rTPJ during mentalizing tasks has been found to correspond to the severity of autistic symptoms and social impairments [18, 19].

To date there is no causal therapy for ASD and treatment typically consists of psycho-educational approaches and pharmacological interventions for comorbid psychiatric disorders [2]. In the absence of causal treatment, it appears crucial to explore the underlying neurobiology and investigate interventions that may have an impact on brain function in ASD. Here, one important avenue of research is targeting the neurocognitive pathway of mentalizing by means of NIBS in order to facilitate ASD individuals´ inferences regarding other peoples’ mental states [20]. While previous research has provided proof-of-principle evidence that repetitive transcranial magnetic stimulation (rTMS) of the mentalizing pathway can modulate social abilities in patients with ASD, the results of NIBS studies with ASD individuals have not been consistent [6, 21–29]. Still, the majority of the few existing studies investigated the effects of rTMS over the dorsolater prefrontal cortex (dlPFC) attempting to induce NIBS effects on executive functions, but showed no improvement in social deficits [21–25]. Only few TMS studies in small cohorts have targeted other regions of the mentalizing pathway such as the DMPFC or the medial prefrontal cortex (mPFC) [10, 25]. For example, Enticott et al. examined adults with ASD without intellectual impairment with deep rTMS over the DMPFC [28]. Participants showed a reduction in social relating impairment, while no significant effects for the experimental tasks were observed [30]. Avirame et al. reported in a case report that two ASD individuals, who were treated with deep TMS over the mPFC showed improvement in sociability and communication skills [31].

The TPJ, a hub of the ‘neurocognitive pathway of mentalizing’, is a region that has been shown to be under-active in autism and is also functionally coupled with the dmPFC [10, 13, 32, 33]. Besides, the TPJ is due to its location close to the midline structures well accessible for applying TMS. Consequently the TPJ could function as an important and accessible entry point of the neural network that is relevant for processing social cues.

Previous research using NIBS for treatment of depression has repeatedly demonstrated that variation of the stimulation site drastically affects outcome, which makes precision tools indispensable to reduce error and increase response rates [34, 35]. NIBS depression studies discuss currently the benefits of using functional neuroimaging to define the stimulation targets in such a way that relevant networks can be modulated at the individual level [36]. Moreover, brain activation levels vary more strongly between subjects, whereas structural landmarks (i.e. gyri and sulci) do not show this variability [37]. Following this rationale, we implement fMRI-guided TMS in our study. Besides, a newer form of rTMS protocol known as intermittent theta-burst-stimulation (iTBS) has been shown to produce at least similar, if not greater, stimulation effects than traditional rTMS. This protocol has a shorter stimulation duration than conventional rTMS and produces electrophysiological and behavioural changes that outlast the period of stimulation by more than 60 min [38]. Combining this stimulation protocol with fMRI-guided target selection and stereotactic neuronavigation, which allows to track the target in the individual participant, results in a state of the art precise stimulation of the defined target [34, 35].

### Objectives

To optimally probe the effects of rTMS in the rTPJ in ASD, we will combine the afore mentioned state-of-the-art stimulation techniques, including individualized fMRI-guided targets, time-efficient intermittent theta-burst-stimulation (iTBS) and a stereotactic neuronavigation.

In our study on the basis of the current literature the neurocognitive pathway of mentalizing will be localized using a well-established video-based fMRI task, which contrasts brain activation during scenes with socially engaging vis-a-vis socially neutral content [39]. This has been shown to consistently localize activation maxima in regions involved in social cognition including the dmPFC and TPJ on the single-subject level [39]. In a second session, each participant’s activation maximum in the rTPJ will be used as a stimulation target to conduct a neuronavigated iTBS intervention with the aim of modulating social information processing. The effects of the stimulation will be measured by using a test battery encompassing social cognitive as well as cognitive control tasks.

We hypothesize that adults with ASD without intellectual impairment will show an iTBS-induced improvement in social information processing, measured by an established probabilistic learning task that requires the integration of both social and non-social information [40]. In particular, participants with ASD without intellectual impairment belonging to the treatment group will show an increased ability to integrate social information into their decision-making process compared to the control group. We hypothesize that these effects are not due to changes or baseline differences in executive functioning.

Secondary analyses will investigate group differences in executive function tests as well as brain activation and connectivity in the ASD and control group.

## Methods

### Study design and ethics approval

Our study is a single-blind, between-subject, sham-controlled, neuroimaging-guided brain stimulation study, exploring the effects of non-invasive brain stimulation on social cognition and executive function in individuals with ASD without intellectual impairment in comparison to control participants without ASD. Participants will be randomly assigned using block randomization to one of the two stimulation conditions (verum vs. sham) in the beginning of the study. Participant recruitment, neuroimaging, brain stimulation and data collection will be carried out at the Department of General Psychiatry 2 at the LVR-Klinikum Duesseldorf in collaboration with the Institute of Systems Neuroscience, University Hospital Duesseldorf, Germany. Participants will be recruited via advertising flyers, online advertisements and social media. Additionally, participants with ASD will be recruited via the Clinic for Disorders of Social Interaction at the Department of General Psychiatry 2 at the LVR-Klinikum Düsseldorf. This study has been approved by the Ethics Committee of the Medical Faculty Duesseldorf of the Heinrich-Heine-University (ethics approval number: 2021 − 1440), conforms to the requirements of the World Medical Association´s Declaration of Helsinki and is registered at the German Clinical Trial Register (DRKS-ID: DRKS00028819). Written informed consent will be taken by all participants, before entering the study and before any assessments or intervention related to the study are undertaken. Participants will be free to withdraw at any time. If a participant has a legal guardian, informed consent will also be obtained from this person.

### Sample size calculation

A power analysis with an estimated effect size of 0.3, a power of 0.8 and an alpha error of 0.05 was used to determine the required sample size for this study using G* Power [41]. Based on this analysis 90 participants are required. In order to divide the participants in four groups a total sample of 92 participants is required. Taking possible drop-outs as well as loss of data due to technical problems into account we have decided to include 52 participants in each arm of the study, i.e. 52 participants with ASD and 52 participants without ASD. Only little prior evidence exists in the field of neuronavigated TMS in adults with ASD, so that no prior studies could serve as a basis for the power analysis. Since this is a proof-of-concept study we opted for a small effect size, so that even smaller effects of the intervention can be detected.

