An important strength of this study will be its relatively large sample size. As already mentioned, the few existing TMS studies in adults with autism have had relatively small sample sizes [29]. Our target of 104 participants will ensure statistical power to test our hypothesis. Another strength of the current study is the use of neuronavigation to localize the personalized target, which ensures accurate and consistent targeting of the region of interest, thus minimalizing variability and increasing validity of our findings. Furthermore, the utilization of iTBS is a strength, as it offers a more time-efficient and potentially more effective stimulation paradigm [38]. A limitation of this study could be employing only a single session of TMS, as multiple sessions could yield cumulative effects and better measurable results. Another limitation could be the single-blind study design. However, the primary endpoint tasks are highly standardized and the entire evaluation process is computerized, thereby minimizing any effects arising from the lack of blinding.

If this study succeeds in demonstrating that personalized TMS can modulate social cognition in adults with ASD without intellectual impairment, this may serve as an important stepping stone towards studies with larger sample sizes, more TMS sessions and maybe different TMS protocols.

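### N = 90 matches an effect of f = 0.3 (0.6 SD) tested on the whole sample; this is not a small effect, and the 80% power does not carry over to the ASD verum-versus-sham hypotheses

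*Protocol article*

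**What the plan says.** Under Sample size calculation, the protocol article reports "A power analysis with an estimated effect size of 0.3, a power of 0.8 and an alpha error of 0.05", computed in G*Power. It concludes: "Based on this analysis 90 participants are required". This becomes 92 so that four groups can be formed, and then "52 participants with ASD and 52 participants without ASD" to allow for losses. The section does not say whether 0.3 is f, d or another metric, nor which test was powered. It describes the choice as follows: "we opted for a small effect size, so that even smaller effects of the intervention can be detected". The Discussion adds: "Our target of 104 participants will ensure statistical power to test our hypothesis".

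The Objectives place the main hypothesis in ASD. Participants with ASD "belonging to the treatment group will show an increased ability to integrate social information into their decision-making process compared to the control group". Outcome measures repeats the ASD restriction for facial recognition (ASD verum against ASD sham) and for correct responses and following of social cues in the learning task. The same section also states one hypothesis, on the social weighting parameter, without restricting it to ASD. The Analysis plan names two-way factorial ANOVAs for the behavioural tasks. For the learning-model parameters it names mixed ANOVAs with group and stimulation as between-subject factors.

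**The concern.** Two affirmative statements need checking against the plan's own figures: that the trial was sized for a small effect, with still smaller ones detectable, and that 104 participants secure power for the hypothesis. If 0.3 is Cohen's f, it is a sizeable standardised difference. If the hypothesis concerns verum against sham among ASD participants only, half of the sample does not enter that comparison. A reader who takes both statements at face value could give a null result in ASD more weight than the design allows.

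**Working it through.** **Inputs.** From Sample size calculation: effect size 0.3, power 0.80, alpha 0.05, N = 90, 92 and 104. Assumed, because not stated: 1:1 allocation to verum and sham (23 per cell at 92, 26 per cell at 104) and two-sided t tests.

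**1. Reproducing N = 90.** The noncentral F with λ = f²N, 1 numerator df, 4 groups and f = 0.3 gives:

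| N | λ = 0.09 × N | Power |
|---|---|---|
| 89 | 8.01 | 79.9% |
| 90 | 8.10 | 80.3% |
| 92 | 8.28 | 81.2% |
| 104 | 9.36 | 85.8% |

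The smallest N reaching 80% is 90, an exact match; using 2 groups gives the same N. Other readings:
- 3-df test over four groups: 126.
- Two-sample d = 0.3, two-sided: 176 per arm, 352 in total.
- Correlation r = 0.3: about 85.
- Repeated-measures variants tried: 17 to 95, none giving 90.
- Paired or one-sample t test with dz = 0.3: also 90, but it does not compare verum with sham.

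**2. Size of f = 0.3.** For two equal groups d = 2f = 0.6. The usual benchmarks for f, which the article does not give, are 0.10 small and 0.25 medium. For 80% power with 1 df, f = 0.25 needs 128 participants and f = 0.10 needs 787. Power at f = 0.10 is 15.8% with 92 and 17.3% with 104.

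**3. ASD verum versus ASD sham, d = 0.6.** The noncentrality is d√(n/2).

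| Per arm | Noncentrality | Power, ASD data only | Power, pooled four-cell error | d for 80% power (ASD data only) |
|---|---|---|---|---|
| 23 | 0.6 × √11.5 = 2.03 | 51.2% | 52.1% | 0.84 |
| 26 | 0.6 × √13 = 2.16 | 56.4% | 57.2% | 0.79 |

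At d = 0.3 the power is 17-19%. For 80% power at d = 0.6 this contrast would need 45 per arm, that is 90 ASD participants.

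**4. Group-by-stimulation interaction.** In a balanced 2 × 2 design the difference of differences is 4f SD.
- If f = 0.3 was meant for the interaction and controls do not respond, the effect in ASD is 4 × 0.3 = 1.2 SD. ASD verum versus sham then has 98-99% power.
- If the effect is 0.6 SD in ASD and zero in controls, f = 0.6/4 = 0.15, and interaction power is 30% (N = 92) to 33% (N = 104).
- At N = 104, 80% power needs f = 0.277, a difference of differences of 4 × 0.277 = 1.11 SD.

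**5. Baseline adjustment of the learning task.** With pre-post correlation ρ, the effective d is 0.6/√(1 − ρ²). No ρ is given, so these values are assumed:
- ρ = 0.5: d = 0.69, power 63% (23 per arm) to 69% (26 per arm).
- ρ = 0.7: d = 0.84, power 80% to 84%.

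**The case against.** The strongest reply is that nothing is miscalculated. N = 90 is correct for a 1-df effect, and every main effect and the interaction in the planned two-way ANOVA has 1 df and uses all participants. The social-weighting hypothesis carries no ASD restriction, so a whole-sample stimulation effect is one legitimate target, with 80-86% power at f = 0.3. This stands, and it means the Discussion's assurance can be true for one hypothesis.

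A reader might go further and infer that the key contrast simply has about half the power claimed, or that only effects near 0.8 SD can be found. The documents do not support that as fact. The metric is inferred from the match with 90, and 51-57% carries d = 0.6 from the whole sample into ASD. If 0.3 was the interaction effect with no response in controls, power in ASD would be 98-99%. A one-sided test would give 64-69%. The learning task is given before and after stimulation, so adjustment could give 63-84% at assumed correlations of 0.5-0.7. However, the sample-size text does not invoke adjustment, and the Analysis plan lists no pre/post factor. Adjustment also cannot help facial recognition, which is measured only after stimulation.

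None of this rescues the word small. The interaction reading makes the assumed effect larger still, and a d of 0.3 would need 352 participants.

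It might also be said that such detail belongs in the analysis plan. The point here is what the article asserts, not what it leaves out.

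**Conclusion.** The point holds in limited form, as a should-fix.

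- **Effect size.** The statements that the assumed effect is small and that smaller ones can be detected are not supported. This rests on reading 0.3 as f, which reproduces 90 exactly. Only the label depends on outside benchmarks; the conversion to 0.6 SD does not.
- **Which effect is powered.** The 80% belongs to a whole-sample 1-df effect. That may suit the unrestricted social-weighting hypothesis, but it does not carry over to the ASD verum-versus-sham hypotheses.
- **Size of the gap.** For those hypotheses power is 51-57%, on condition of 1:1 allocation, a two-sided test, d = 0.6 in ASD and no baseline adjustment.

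The calculation itself is not wrong, and the material does not show that the sample must grow.

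**What to change.** Keep 104 participants and change the text:

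1. In Sample size calculation, name the metric and the test. If it is as inferred, this is Cohen's f = 0.3, equal to d = 0.6 for a verum-sham main effect, in a 1-df F test on all participants.
2. Delete the wording that calls the effect small and says smaller ones can be detected.
3. Add power and minimum detectable effect for ASD verum versus ASD sham: with 26 per arm, about 56% at d = 0.6, and d of about 0.79 for 80% power, unadjusted. For the interaction, give a difference of differences of about 1.1 SD at N = 104. State the assumptions: 1:1 allocation, two-sided test, no baseline adjustment. If adjustment is planned for the learning task, give the assumed pre-post correlation.
4. In the Discussion, limit the sentence on power to the effect actually powered.

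The cost is wording only. Design, recruitment and analysis are unchanged, and the stated power becomes less favourable for the ASD contrast.

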### Inclusion/exclusion criteria

Participants with an already confirmed ASD diagnosis will be included if they: (1) are 18 to 65 years of age, (2) have not a contraindication for an MRI scan, (3) have an AQ-score equal to or greater than 28, (4) have an IQ greater than 80 and (5) have a BDI II score less than 20. Healthy controls with no history of psychiatric disorders and no psychiatric symptoms as assessed by an experienced consultant psychiatrist during the screening interview will be included if they: (1) are 18 to 65 years old, (2) have not a contraindication for an MRI scan, (3) have an AQ-score equal to or less than 27, (4) have an IQ greater than 80 and (5) have a BDI II score less than 20.

General exclusion criteria will be: (1) known epilepsy, (2) intracranial metallic foreign bodies, intracranial implants and big head tattoos, (3) significant brain malformations, brain tumors, cerebrovascular events (strokes), traumatic brain injuries, neurodegenerative diseases and brain surgeries, (4) implanted cardiac pacemaker, (5) severe illness, (6) tinnitus, (7) glaucoma, (8) pregnancy, (9) medication affecting the seizure threshold, (10) claustrophobia, 11) current or previous treatment with Deep Brain Stimulation or Vagus nerve Stimulation, 12) heavy alcohol consumption (> 60 g alcohol per day) or substance abuse, 13) limited knowledge of German language.

### Experimental procedure

An overview of the study plan is depicted in Fig. 1. At the beginning, all participants will undergo a screening session conducted by an experienced psychiatrist so that inclusion/exclusion criteria can be assessed and necessary information can be reviewed. Afterwards informed consent will be obtained and as a part of the screening the medical history will be taken, the Autism Spectrum Quotient (AQ), the Intelligence Quotient (IQ) measured using the multiple-choice vocabulary intelligence test MWT, the Beck Depression Inventory (BDI II) score, the Edinburgh handedness inventory score, as well as sociodemographic data will be collected [42–45]. The data from the screening session will be used in secondary analysis. Participants will be randomly assigned to one of the two stimulation conditions, i.e. verum-iTBS or sham-iTBS. The entire sample will therefore include four groups (ASD individuals receiving verum-iTBS, ASD individuals receiving sham-iTBS, controls receiving verum-iTBS and controls receiving sham-iTBS). All participants will receive an anatomical MRI scan, including a T1-weighted sequence as well as an fMRI scan. During the fMRI scan a well-established video-based social perception task (social localizer) will be administered [39]. In this paradigm audiovisual movie clips displaying pre-selected social clues are presented in order to detect the brain networks subserving perception. Based on this localizer, activation maxima in rTPJ will be extracted at the single-subject level, which will be then used as personalized targets for the neuronavigated iTBS session. Coil positions will be navigated using a frameless stereotaxic neuronavigation system (Localite GmbH). This allows to co-register T1 images of the participants with their anatomical landmarks, enhancing the precision of the stimulation over the fMRI-derived activation peaks of the rTPJ. For the iTBS the following protocol will be used: 600 pulses will be given in 1,84 s trains repeated every 10 s for a total of 189 s at an intensity of 70% of the motor threshold. Stimulations will be performed with a PowerMAG Research 100 stimulator (MAG and More GmbH) and a PMD70-aCool coil (verum-iTBS) as well as a PMD70-aCool-Sham coil (sham-iTBS). Directly after stimulation, the following tasks will be administered in the following order: (1) probabilistic learning task, (2) a facial recognition paradigm, (3) coin rotation task and (4) 3-back task [40, 46–48]. The estimated time required to complete these tasks is approximately 35–40 min. The time of completion of the TMS, as well as the start times of each task, will be recorded. There will be a maximum of 5 min between the completion of the TMS and the start of the social probabilistic learning task. As a result, all tasks will be completed within approximately 40–45 min after the completion of the TMS.
